#### Manual content

The CaFI intervention includes five key components:
*Engagement and assessment [two sessions]*
In the development phase, participants stressed the importance of taking time to build trust given the history of negative relationships between African-Caribbeans and statutory mental health services. Accordingly, in these initial sessions, the emphasis will be on trust-building and engagement, developing a positive therapeutic relationship, and establishing working therapeutic alliance between family members. Therapists will undertake a thorough assessment of the family; identifying strengths and resources as well as a formulation of needs. Additionally, explanation of the intervention is provided (including proposed structure and purpose and potential benefits to the family), problems identified and prioritised based on the family’s wishes and formulation, realistic SMART (specific, measurable, attainable, relevant, timely) goals and expectations for future session set.
*Shared learning [two sessions]*
‘*Shared learning*’ is a collaborative approach to psycho-education designed to facilitate engagement and alliance. This approach allows the therapist, relatives and service user to learn from each other’s experiences and acquire knowledge that will lead to more beneficial ways of managing difficulties related to schizophrenia and psychosis in the family. This is an important aspect of cultural-adaptation for this ethnic group; particularly in terms of addressing illness beliefs and explanatory models. In conjunction with initial assessment, these sessions lay the groundwork for other components of the intervention and behaviour change.
*Communication [two sessions]*
The ‘*communication*’ sessions support service users and relatives to communicate more effectively with each other and with service providers. The emphasis on understanding ‘*how the system works*’ and developing communication and advocacy skills was regarded by participants as a highlighting culturally-specific difference between the needs of African-Caribbeans and other groups. Additionally, as when working with other groups, therapists will be expected to model and positively reinforce effective communication skills, including establishing ground rules for good communication from the outset. The specific communication skills to be addressed with each family will be decided collaboratively with the family members based on the initial assessment and formulation. Developing good communication skills lays down an important foundation for subsequent sessions on problem solving and goal setting.
*Stress management, coping and problem Solving [two sessions]*
These sessions focus on helping both service users and relatives to manage current stressors through joint problem-solving or other ways of coping that may help reduce family tension. These sessions flow from and complement the previous session on communication. As communication difficulties can be a significant source of stress for families, improved communication can help families work more collaboratively to solve problems.
*Maintaining gains and staying well [two sessions]*
The aim of the final two sessions is to review and consolidate the material that has been covered over the preceding sessions and to develop a plan for staying well as a family and reducing the risk of further relapse. To make these sessions more culturally-appropriate, the focus will be on recovery, emphasising strengths and aspirations, and the importance of having an agreed crisis plan to improve care pathways by reducing the likelihood of police involvement and coercive care. Therapists will establish what recovery means for each family; help them set realistic expectations for positive, on-going change; and address any difficulties the family might experience with endings. Providing the family with a ‘goodbye letter’ is an important opportunity for the therapist to give positive feedback on the family’s strengths and hard work in therapy; thereby reinforcing therapeutic engagement and alliance.

#### Duration and intensity of therapy

CaFI is designed to be conducted over ten sessions as recommended by NICE (2014). To allow families to work on issues outside the session and facilitate potential absence or illness; CaFI will be delivered over approximately 20 weeks. The pace of the sessions will depend upon the needs of the family and may be arranged weekly initially to facilitate engagement and cover core components but subsequently, towards the end of therapy, might be reduced to fortnightly or longer. Each session will last around 1 h (in practice, 1.5 h with an additional 30-min preparation and debriefing).

## Data collection

### Quantitative data

#### Feasibility and acceptability of recruitment and delivery

We will assess the feasibility of delivering CaFI, including attendance, attrition (number of drop-outs at each time point), and retention (the proportion of participants who complete therapy sessions). Therapists will record session attendance and retention data to measure feasibility of delivery (i.e. location, duration, intensity, attendees). Participants (service users and biological family members/FSMs) will be asked to complete evaluation/feedback forms at the end of each session to monitor the acceptability of the intervention.

We shall assess the feasibility of undertaking research on CaFI, by studying recruitment (the proportion of eligible participants consenting to join the study) and completeness of outcome measurement. Data will be collected on reasons for ineligibility and non-consent; including anonymous information on gender, ethnicity and date of birth for those who are approached but do not consent to take part. We shall record and compare recruitment rates across different referral sites (inpatient, community, third sector) and sources (CRN, research team, self-referral, clinical referral).

### Outcome measures for future RCT design

To identify outcome measures for future randomised controlled trials (RCTs) and assess the feasibility of collecting them; participants (service users and biological family members/FSMs) will complete a range of quantitative outcome measures at baseline, post-intervention and 3-month follow-up. These will be conducted by trained RAs who are independent from the delivery of the therapy. Where participants leave the intervention early, we shall attempt to gather outcomes at exit and 3-month follow-up. Assessing feasibility of collecting these measures will be important to inform a later trial and economic evaluation.

#### Socio-demographic questionnaire

A self-report socio-demographic questionnaire to collect data on key variables such as age, gender, ethnic group and religion will be completed by service users, family members and FSMs. Additional questions for service users will include diagnosis, relationship with the family member/FSM, length of time since first contact with services, inpatient history and medication.

### Service user and family outcome measures

#### Psychosis symptom severity (service users)

Tables 1 and 2 show the patient and family measures used in the study and outlines the data collection schedule. The *Positive and Negative Syndrome Scale* (PANSS) [52] is a widely used 30-item semi-structured interview designed to assess positive, negative and general symptoms in service users with schizophrenic spectrum diagnoses. The PANSS has good psychometric properties of reliability and validity and is sensitive to change [52, 53]. Two trained RAs will rate the PANSS and we will report inter-rater reliability.

**Table 1 Tab1:** Patient assessment schedule

Assessment tool	Brief description	Time point			
		Duration (min)	Baseline	Post-CaFI	3-month follow-up
Socio-demographic	Socio-demographic	5	x		
PANSS	Symptoms	30–40	x	x	x
PSP	Personal and social functioning	5	x		x
PCS	Perceived criticism	5	x	x	x
Brief-IPQ	Illness beliefs	5	x		
EQ-5D	Economic evaluation	5	x	x	x
WAI—short form	Working alliance/engagement	5	x	x	x
Qualitative interview	Acceptability and feasibility	30–45			x
Total time burden			60–80	45	80–95
Session feedback forms	Acceptability	5 min end of each session			
WAI—short form Session 3	Therapeutic alliance	5 min complete during session 3			
Relapse	Case notes 40 weeks before, during and 40-week post-intervention	0 min—undertaken by independent review at 3-month FU

**Table 2 Tab2:** Family member/family support member (FSM) assessment schedule

Assessment tool	Brief description	Time point			
		Duration (min)	Baseline	Post-CaFI	3-month follow-up
Socio-demographic	Socio-demographic	5	x		
GHQ—short form	Stress/burden	5	x	x	x
KAPI—relatives^a^	Knowledge about psychosis	15–30	x	x	x
Brief-IPQ^a^	Illness beliefs	5	x		
EQ-5D	Economic evaluation	5	x	x	x
Qualitative interview	Acceptability and feasibility	30–45			x
Total time burden			35–50	25–40	55–70
WAI—short form Session 3	Therapeutic alliance	5 min complete during session 3			
Session feedback forms	Acceptability	5 min end of each session			

^a^Biological family members and nominated FSMs only (not recruited FSMs)

#### Social functioning (service users)

The *Personal and Social Performance Scale* (PSP) [54] is a 100-point, observer-rated, single-item scale. The scale measures social functioning across the past month in four areas: socially useful activities (including work and study, personal and social relationships, self-care and disturbing and aggressive behaviours. It is reliable, valid and sensitive to change and correlates with PANSS scores [55]. Ratings will be made by the RA on the basis of service users’ reports of symptoms, service users’ behaviour during PANSS interviews, and reports from care staff and significant others. PSP data will be collected at baseline and 3-month follow-up only.

#### Perceived criticism (service users)

The *Perceived Criticism Scale* (PCS) [56] is a 4-item self-report measure of service user perceptions of relatives’ criticism. It provides an efficient way of assessing negative aspects of the psychosocial environment. The PCS is a reliable and valid measure [57, 58] and perceived criticism has been shown to predict symptom course, treatment outcome and relapse in schizophrenia [44, 57]. Service users will be asked to complete this measure in relation to their family member/FSM. If there is more than one biological family member/FSM taking part in the intervention, the service user will be asked to rate the person who is currently the most important to them and with whom they share the closest relationship.

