*Recruited*: Service users who are unable to nominate anyone but wish to participate will be given the opportunity to select a FSM from a pool of community volunteers who have been specifically recruited for this study. Nine FSMs have been successfully recruited using extensive public engagement via local media (community radio, newspaper), posters and flyers and by delivering presentations at third sector organisations and community settings frequented by large numbers of African-Caribbeans, such as Black-majority churches. Potential FSMs met with the RA to determine their suitability and were fully briefed about the study (PIS) before providing informed consent to undertake the role.Recruited FSMs have been given honorary contracts to work at Trust sites, which involved obtaining Disclosure and Barring Service checks, signing confidentiality agreements and completing occupational health checks. They received one-day Cultural Competency training delivered by *Just Psychology* [44] (Feb 2015) and a 2-h training session facilitated by the PI and RA on the research protocol and the FSM role (Mar 2015). Each FSM wrote a brief biography and described their interest in undertaking the role. This information will be given to service users to help them decide which FSM they would like to work with. Once the FSM has been matched to a service user, an initial meeting will be scheduled to conduct baseline assessments.

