#### Knowledge about psychosis (biological family members/nominated FSMs)

The *Knowledge about Psychosis Interview* (KAPI) [63] is a revised version of the *Knowledge about Schizophrenia Interview* (KASI) [21]. The KAPI will not be conducted with recruited FSMs at baseline as they will have limited knowledge of the service user’s problems before the intervention. As KASI and KAPI are culturally-insensitive and use outdated language; we are currently developing and validating two updated versions of these instruments: (1) the Knowledge About Psychosis (KAP) questionnaire, for use in a general population sample; and (2) the Culturally-adapted Knowledge About Psychosis (CaKAP) questionnaire, which has been adapted for the African-Caribbean community ([name] et al., in prep). It is anticipated that the questionnaire(s) will be available for use in future RCTs.

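### Perceived Criticism Scale: the rated person may differ between visits where several members take part, and recruited volunteers are rated with little or no prior relationship at baseline

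*Protocol article*

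**What the plan says.** The section on perceived criticism describes the PCS as a "4-item self-report measure of service user perceptions of relatives’ criticism". The default referent is the participating member: "Service users will be asked to complete this measure in relation to their family member/FSM". A choice arises only under a condition, "If there is more than one biological family member/FSM taking part in the intervention", and then "the service user will be asked to rate the person who is currently the most important to them"; the same sentence adds closeness of the relationship.

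Table 1 schedules the PCS at baseline, post-CaFI and 3-month follow-up, in line with the general statement that participants "will complete a range of quantitative outcome measures at baseline, post-intervention and 3-month follow-up".

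FSMs are either nominated by the service user or recruited by the study. A service user who cannot nominate anyone "will be given the opportunity to select a FSM from a pool of community volunteers who have been specifically recruited for this study". For these volunteers, "The KAPI will not be conducted with recruited FSMs at baseline as they will have limited knowledge" of the service user's problems, and the footnote to Table 2 restricts both the KAPI and the Brief-IPQ to biological relatives and nominated FSMs. Table 1 has no corresponding note for the PCS.

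The Data analysis section says that the variability of the outcome measures will be estimated to inform the sample size of a future trial.

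**The concern.** A change score on a measure of one relationship is interpretable only if the same relationship is rated each time. The rule for families with several participants is worded in the present tense and is not tied to the baseline choice. CaFI works directly on communication and tension within the family, so who is closest could shift during the study. If the rated person changes, the difference between two people enters the change score as apparent change or as noise. If the identity is not recorded, no later analysis can separate the two.

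The second issue concerns recruited FSMs. A baseline rating of a volunteer who is newly met or not yet met is not a rating of an existing family relationship. It therefore cannot serve as a pre-intervention value in the way a rating of a relative can.

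At stake are two stated purposes of the study: judging which measures suit a later trial, and supplying the variability for its sample size.

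**Working it through.** **1. Which service users are affected.** With one participating relative or nominated FSM, the PCS refers to the same existing relationship throughout, and neither issue arises. The first issue is confined to service users with several participating members; the second to those with a recruited FSM. The document gives neither share. Nine volunteers have been recruited. If each is matched to one service user, the share is at most 9/30 = 30%; the document does not state that limit.

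**2. What the volunteer relationship is at baseline.** The paragraph on recruited FSMs says "Once the FSM has been matched to a service user, an initial meeting will be scheduled to conduct baseline assessments", which most naturally describes the FSM's own assessments in Table 2. The service user's baseline, which contains the PCS, takes place at the consent meeting or one further meeting (Participants and recruitment procedures) and is not linked to matching. So the volunteer may be newly met or not yet met. This is an inference from the two passages; the document does not say it.

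**3. The plan's own figure.** The only sample-size figure is n = 30: 150 eligible × 1/3 consenting = 50, which is at least 30. It reproduces and is not in dispute. No SD, correlation or target is stated for the PCS.

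**4. Change of rated person (illustration; all inputs assumed).** Let ρ be the between-visit correlation for the same rated person, ρ₀ that for different persons, and s the share of the whole sample whose rated person changes. With equal variances σ² at both visits:

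- r = (1 − s)ρ + sρ₀
- Var(change) = 2σ²(1 − r)
- ratio to a fixed referent = (1 − r)/(1 − ρ)

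Taking s from 10% to 30% and ρ₀ from 0 to 0.3:

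- ρ = 0.5. Lowest (s = 0.1, ρ₀ = 0.3): r = 0.48, ratio 0.52/0.50 = 1.04. Highest (s = 0.3, ρ₀ = 0): r = 0.35, ratio 0.65/0.50 = 1.30.
- ρ = 0.7. Lowest: r = 0.66, ratio 0.34/0.30 = 1.13. Highest: r = 0.49, ratio 0.51/0.30 = 1.70.

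For a future two-arm trial analysed on change, with an assumed effect of 0.5 baseline SD, 90% power and two-sided 5%, n per arm rises from 85 to between 88 and 110 (ρ = 0.5), or from 51 to between 58 and 86 (ρ = 0.7).

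Only multi-member families can contribute to s, so 30% of the whole sample requires at least that share of such families.

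**5. Recruited FSMs in a pooled baseline variance (illustration; all inputs assumed).** Let q be their share, k the ratio of their SD to the relatives' SD, and d the difference in means in relatives' SD units.

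- pooled variance / relatives' variance = (1 − q) + qk² + q(1 − q)d²

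With q from 10% to 30%, k from 0.25 to 0.5 and d from 0.5 to 1.5:

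- Lowest (q = 0.3, k = 0.25, d = 0.5): 0.700 + 0.019 + 0.053 = 0.77.
- Highest (q = 0.3, k = 0.5, d = 1.5): 0.700 + 0.075 + 0.473 = 1.25.

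The ratio falls on both sides of 1, so even the direction is not determined.

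**6. Against sampling error.** For normal data, the 95% interval for a variance from n = 30 runs from 29/45.7 = 0.63 to 29/16.0 = 1.81 times the estimate. All the ratios above lie within it.

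**The case against.** The strongest reply is that the article is silent rather than wrong. The word 'currently' appears once, with no visit rule, and an instruction to carry the baseline referent forward may well stand in the full protocol or the assessor's forms. Rating whoever is closest now is also defensible for a scale meant to capture the psychosocial environment. Nothing commits the study to one pooled PCS summary, and breakdown by family type usually belongs in the analysis plan. Finally, the illustrated distortions are no larger than the sampling error of a variance from 30 people.

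Much of this stands. A reader might infer that the referent is chosen afresh at every visit; the text permits that but does not say so. A reader might also take the KAPI exemption as proof that the authors saw the same problem. The parallel is only partial: the KAPI is answered by the FSM and the PCS by the service user. It shows that a recruited FSM starts with little knowledge of the service user, and no more.

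What does not stand is that the matter can wait for analysis. The article chose to state the referent rule, and the rule as stated leaves the person open across three visits. Reporting by family type can be settled later, but an unrecorded identity cannot be recovered. Nor does imprecision at n = 30 excuse an avoidable distortion, which is added to that imprecision.

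**Conclusion.** The point holds in a limited form. For service users with several participating members, the stated rule allows the rated person to differ between visits, and no record of that person is mentioned. For service users with a recruited FSM, a measure of relatives' criticism is applied at a baseline where there may be little or no relationship to rate. PCS change and variability estimates that include these groups may mislead a future sample-size calculation.

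The size cannot be derived from the document. The factors of 1.04 to 1.70 for change variance and 0.77 to 1.25 for pooled baseline variance rest wholly on assumed correlations, shares, SD ratios and mean differences. No stated figure, including n = 30, is wrong.

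Two stronger readings are tempting and unsupported. One is that volunteer ratings must begin near the floor of the scale and can only rise, which would look like worsening. The article gives no PCS range or scoring and no expected score for volunteers. The other is that pooling must overstate the variance; the check shows that it can also understate it.

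**What to change.** - In the PCS section and the assessor's instructions: where more than one member takes part, have the service user name one index person at baseline, record that identity and the family type, and rate the same person at all three time points. Record the reason if that becomes impossible.
- Report PCS means, SDs and between-visit correlations separately for biological relatives, nominated FSMs and recruited FSMs.
- State that baseline PCS for a recruited FSM is not to be read as describing a pre-existing relationship.
- Choose the planning figures to match the family types that the future trial will include. Leaving recruited FSMs out of those figures altogether would be right only if that trial leaves them out too; delivery through FSMs is one of this study's objectives.

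The cost is one instruction and one extra data field. The downside is smaller numbers behind each PCS summary; with nine volunteers at one service user each, the recruited-FSM group would be at most nine, so its SD and correlations would be very imprecise.

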#### Illness beliefs (service users, biological family members/nominated FSMs)

A 12-item modified version of the Brief Illness Perception Questionnaire (Brief-IPQ) [59] will be used to assess illness perceptions in service users and family members/nominated FSMs at baseline. The Brief-IPQ, like the original IPQ (Addington, 2003) from which it was derived, were designed for physical health problems but can be adapted for mental health problems (Lobban et al. 2005; Lobban et al. 2013). Modifications for this study are coherent with previous adaptations for mental health (Lobban et al., 2013) and include replacing the word ‘illness’ with ‘mental health problems’ and adding three items that assess the following: personal effort (how much effort the individual is making to help them get well); cause internal (the extent to which the symptoms are caused by the individual’s behaviour); and self-blame (the extent to which the individual is to blame for the mental health problems). The Brief-IPQ has demonstrated good reliability and validity [59] and has previously been used in psychosis research e.g. [60–62].

#### Knowledge about psychosis (biological family members/nominated FSMs)

The *Knowledge about Psychosis Interview* (KAPI) [63] is a revised version of the *Knowledge about Schizophrenia Interview* (KASI) [21]. The KAPI will not be conducted with recruited FSMs at baseline as they will have limited knowledge of the service user’s problems before the intervention. As KASI and KAPI are culturally-insensitive and use outdated language; we are currently developing and validating two updated versions of these instruments: (1) the Knowledge About Psychosis (KAP) questionnaire, for use in a general population sample; and (2) the Culturally-adapted Knowledge About Psychosis (CaKAP) questionnaire, which has been adapted for the African-Caribbean community ([name] et al., in prep). It is anticipated that the questionnaire(s) will be available for use in future RCTs.

